### Follow-Up

Participants will be followed by two experienced researchers every week through phone interviews after discharge. Details of IMT will be documented, quality assessment will be performed, and any reported adverse events will be followed up, with assistance provided if necessary. All of the participants will be asked to return to the clinic for follow-up visits at 30 days post-randomization.

### Objectives

The aim is to assess the effectiveness of IMT by measures including the improvement of inspiratory muscle strength, pulmonary function, and quality of life, and by the avoidance of clinically adverse events. We will also assess the feasibility of IMT by examining the safety of training performance and through use of a satisfaction questionnaire.

### Study Endpoints

#### Primary Endpoint

##### Change in Inspiratory Muscle Strength

Static MIP will be selected for the estimation of inspiratory muscle strength. A standard measurement according to the *ERS Statement on Respiratory Muscle Testing at Rest and during Exercise* published by the European Respiratory Society (ERS) will be taken (14) (Powerbreathe® K5). The MIP test will be performed at baseline and at 30 days post-randomization.

#### Secondary Endpoints

##### Feasibility

Adverse events, heart rate, systolic blood pressure, diastolic blood pressure, and oxyhemoglobin saturation of patients during training while in hospital will be recorded. In addition, the workloads of MIP and the Borg scores will be recorded after every day of training in the hospital. The satisfaction of patients in the IMT group will be evaluated using a questionnaire at discharge and again at 30 days post-randomization (Supplementary Appendix 1).

##### Pneumonia

Pneumonia will be defined as the presence of a new or progressive radiographic infiltrate plus at least two of three clinical features (fever > 38°C, white blood cell count [WBC] > 10 × 10^9^/L or < 4 × 10^9^/L and purulent secretions), based on American Thoracic Society guidelines (15). Events of pneumonia will be followed and recorded by experienced doctors when participants are in hospital. After discharge, participants will be followed by experienced researchers and if a diagnosis of pneumonia is considered possible, guidance will be provided for the patients to complete necessary examinations, until 30 days post-randomization.

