### Invention: IMT

For the IMT group, IMT will be performed for 15 min *per session*, twice a day, with an initial load of 30% of MIP using a threshold inspiratory muscle trainer (c-type, Shengchang medical equipment factory, Yuyao City, China). During the hospital period, the resistance will increase incrementally, based on the rate of perceived exertion scored on the Borg scale (11). If the rate of perceived exertion is <5, the resistance of the inspiratory threshold trainer will then be increase incrementally by 5%. To facilitate training for participants, the load for home-based IMT training will be set at the highest training load achieved while the patient was in hospital. All of the participants will be required to complete maneuvers in the seated position during training, wearing nose-clips. IMT will be performed every day from 12 to 24 h after primary PCI and the final session will be performed 30 days post-randomization. Participants in the control group will receive standard care after primary PCI according to the current clinical practice guidelines (12), which included risk stratification, continuous monitoring and specific nursing. And we also encourage an early ambulation, based on the complications, symptoms, and capacity.

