##### Major Adverse Cardiovascular Events (MACE)

MACE will be defined as all-cause death, recurrence of myocardial infarction, or stroke at 30 days post-randomization.

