##### Length of Stay (LOS)

Length of stay will be assessed by calculating the number of days the patient is in the hospital.

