Previous studies have shown that IMT exceeding 2 weeks of therapy was effective for improving MIP (34), while the efficiency of implementing a shorter training time (< 10 days) still needs further investigation (29, 30, 35). As heart failure is common in patients with AMI, chronic heart failure would play an important role in the study cohort. The present recommendation for patients with heart failure participating in an IMT regimen is to begin with 30% MIP, then gradually increase to 60% MIP, 20–30 min *per session* with 3–5 exercise sessions per week (36). Some large-sample randomized trials have also confirmed the efficiency of these settings (31) and served as the basis of our IMT protocol design.

There are some limitations in our study. First, the present design is a single-center study, and the sample size is relatively small. Second, we selected guideline-based criteria for the diagnosis of pneumonia because no specific criteria have been developed for patients with AMI (15), and the criteria of the Centers for Disease Control and Prevention is not defined. AMI is associated with inflammatory reaction (37), and such a state might reduce the diagnostic power of most common clinical biomarkers. Although a new or progressive radiographic infiltrate and the presence of purulent secretions is the common diagnostic and prognostic indicator of pneumonia (31, 38–40), the significance of fever and white cell count may be limited by the inflammatory stage, which might lead to slightly overall excessive diagnoses (41–43). Third, the important aim of our study is to explore the role of IMT in preventing pneumonia. However, since no high-quality IMT study has been conducted in patients with AMI, we decided to calculate the sample size for our study using inspiratory muscle strength, and later extended this to better explore the effect of IMT on the secondary endpoints, especially pneumonia. Fourth, the model for calculating the risk of pneumonia was based on previous work in patients with ST-elevation myocardial infarction, without validation of its accuracy in our selected patient population (1, 2). Because there are not risk model for pneumonia in patients with AMI currently.

In conclusion, we have considered the significance of this proposed study protocol that was designed to determine the feasibility and potential clinical benefits of IMT in patients with AMI undergoing primary PCI who are at high risk of pneumonia, using a randomized, controlled trial.

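### The pneumonia endpoint has no stated start at randomisation and no rule for pneumonia already present, and length of stay counts earlier days and scores in-hospital death as a short stay

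*Protocol article*

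**What the plan says.** All references are to the protocol article.

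- **Pneumonia, definition.** "Pneumonia will be defined as the presence of a new or progressive radiographic infiltrate plus at least two of three clinical features"; the three features are fever, abnormal white cell count and purulent secretions. No reference time is given for a new infiltrate and no baseline image for a progressive one.
- **Pneumonia, window.** In hospital: "Events of pneumonia will be followed and recorded by experienced doctors when participants are in hospital". After discharge, where pneumonia is thought possible, "guidance will be provided for the patients to complete necessary examinations, until 30 days post-randomization". The end is tied to randomisation; the start is not stated.
- **Length of Stay (LOS).** The whole definition is: "Length of stay will be assessed by calculating the number of days the patient is in the hospital".
- **Major Adverse Cardiovascular Events (MACE), for comparison.** "MACE will be defined as all-cause death, recurrence of myocardial infarction, or stroke at 30 days post-randomization".
- **Study Population.** Patients are already in the cardiac intensive care unit when they qualify. None of the nine exclusions names pneumonia or infection; only the ninth, which is at the researchers' discretion, could cover it.
- **Baseline Characteristics and Medicine.** Chest X-ray and/or CT is provided for diagnosing pneumonia, with repeats if needed, but no time is set.
- **Invention: IMT.** "IMT will be performed every day from 12 to 24 h after primary PCI and the final session will be performed 30 days post-randomization". The time of randomisation relative to admission or PCI is not given.
- **Discussion.** It states that "the important aim of our study is to explore the role of IMT in preventing pneumonia", and that the sample was extended for the secondary endpoints, pneumonia above all.

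**The concern.** Training cannot prevent a pneumonia that exists when the patient is randomised. A prevention endpoint therefore needs a start at randomisation and a rule for cases already present. The article supplies neither, and its exclusion list does not clearly keep such patients out.

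The definition makes this more than a formality. The Discussion concedes that the inflammation of infarction limits the value of fever and white cell count and may lead to some overdiagnosis. Those are two of the three clinical features, and two suffice. With a compatible infiltrate, the criteria can be met very early after infarction, which is the period that the open start fails to rule out.

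Length of stay raises two separate matters. Days before randomisation cannot reflect allocation. And a patient who dies in hospital on day 2 gets a stay of 2 days, which reads as a good result.

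At stake is whether the pneumonia odds ratio and the length-of-stay comparison can be read as effects of allocation to IMT. The primary endpoint is not touched.

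**Working it through.** **1. The plan's own figure.** Inputs from Sample Size Calculation: difference 15, SD 12 cm H2O, two-sided α 0.05, power 0.80. n = 2 × (1.960 + 0.842)² × 12² / 15² = 10.05, rounded up to 11 per group; 11 / 0.8 = 13.75, rounded up to 14. Both stated figures reproduce. (A t-based solution gives 11.09, with power 0.796 at 11.) Neither depends on the pneumonia or stay definitions.

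**2. Expected pneumonias.** The Introduction gives 2–7% for infarction patients in general. 60 × 0.02 = 1.2 and 60 × 0.07 = 4.2, or 0.6 to 2.1 per arm of 30. If one of these were prevalent at randomisation, it would be 1/4.2 = 24% to 1/1.2 = 83% of the expected total. The trial enrols only high-risk patients, so its rate may be higher. At assumed rates of 15% and 30%, the totals are 9 and 18 and one case is 11% or 6%.

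**3. What one case can do (hypothetical).** With 2 events in each arm, the OR is (2/28)/(2/28) = 1.00. If one IMT-arm event was prevalent and that patient leaves the denominator, the OR is (1/28)/(2/28) = 0.50. With two prevalent cases, the chance that both fall in the same arm is 29/59 = 49%.

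**4. Average dilution.** Let p be the total control risk, f the share of it already present at randomisation, and 0.5 the assumed risk ratio for later events. Then IMT risk = p·f + 0.5·p·(1 − f). Neither f nor 0.5 is in the article. With p = 7%:

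| f | IMT risk | RR | OR |
|---|---|---|---|
| 0 | 3.50% | 0.50 | 0.48 |
| 10% | 3.85% | 0.55 | 0.53 |
| 25% | 4.38% | 0.625 | 0.61 |
| 50% | 5.25% | 0.75 | 0.74 |

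The pull is towards 1. Fisher's exact power at 30 per arm is 0.6% at f = 0 and 0.4% at f = 50%, so the matter is interpretation, not power.

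**5. Days before randomisation.** Write stay = A (before) + B (after). A is fixed before allocation, so E[A] is the same in both arms and the expected difference is that of B alone. A can add variance but does not shift the comparison.

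**6. In-hospital deaths.** In a Wilcoxon comparison of 30 with 30, moving one early death from shortest to longest stay changes its comparison with all 30 patients in the other arm, so the rank statistic moves by 30. Its null SD without ties is √(30 × 30 × 61 / 12) = 67.6, so the shift is 30/67.6 = 0.44 SD. With a deaths in one arm and b in the other, all early, the net shift is a(30 − b) − b(30 − a) = 30(a − b). It is zero when a = b.

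**The case against.** The strongest reply is that silence is being read as a rule. The sentence on in-hospital pneumonia says who records events and where. It does not start the count at admission, it speaks of participants, and the same section closes the window by reference to randomisation. The requirement for a new or progressive infiltrate screens out stable earlier disease, the ninth exclusion could be used for active pneumonia, and chest imaging is provided for. The interval before training is probably short. A journal article may also leave time origins and handling of death to the full protocol or SAP.

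Much of this stands. A reader might infer that the plan counts pneumonia from admission; the text does not say so. It only fails to exclude prevalent cases. A reader might also infer that events before the first training session should be removed. That is the wrong anchor: events between randomisation and first training belong in an intention-to-treat comparison, and so does a pneumonia incubating at randomisation that first shows itself later.

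Condensation is not a full answer. The article prints operational definitions, ties MACE to day 30 after randomisation, and prints the exclusion list. Pneumonia is tied at one end only and length of stay at neither. For length of stay, counting earlier days follows from the wording. Whole-admission stay is a legitimate measure, and ranking deaths longest is one option among several, but the printed definition makes an early death look favourable.

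**Conclusion.** The point holds as a gap in two secondary endpoint definitions, of minor to moderate weight. Pneumonia present at randomisation may be enrolled and counted. Days before randomisation are counted in length of stay, and an in-hospital death is scored as a short stay.

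Two stronger conclusions are tempting and not supported. The first is that this biases the trial for or against IMT: prevalent cases and earlier days are balanced in expectation, so the result is dilution and noise. The second is that deaths could reverse the length-of-stay result: the article gives no in-hospital death rate, and the distortion needs deaths to differ by arm, at up to 0.44 SD of the rank statistic per excess early death.

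The share taken by one prevalent case (24% to 83% at 2–7%) is conditional on such a case occurring. Its frequency is not in the article, and the range rests on a general infarction rate. The dilution table rests on assumed values of f and an assumed risk ratio of 0.5. The point deserves action because prevention of pneumonia is named as an important aim and the sample was enlarged with it in view.

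**What to change.** 1. **Pneumonia.** Count only pneumonia whose first qualifying signs or imaging arise after randomisation, up to day 30.
2. **Baseline status.** Record pneumonia or infiltrate present at randomisation as a baseline item, and leave those patients out of the at-risk denominator for this endpoint only. Enter it before the envelope is opened. Because the status is then fixed before allocation, the randomised comparison is preserved.
3. **Length of stay.** Measure from randomisation to discharge alive, rank in-hospital deaths as the longest stays, and compare arms by the Wilcoxon rank-sum test, which Data Analysis already allows. Report in-hospital deaths by arm beside it.

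The cost is some endpoint wording, one baseline field and slightly fewer countable pneumonias. The stated 11 and 14 per group and the total of 60 do not change.

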##### Major Adverse Cardiovascular Events (MACE)

MACE will be defined as all-cause death, recurrence of myocardial infarction, or stroke at 30 days post-randomization.

##### Length of Stay (LOS)

Length of stay will be assessed by calculating the number of days the patient is in the hospital.

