## Discussion

To the best of our knowledge, the proposed protocol is the first study to assess the safety and efficacy of IMT in patients with AMI undergoing primary PCI who are at a high risk of pneumonia during the acute period. Studies have rarely focused on the uncommonly high rate of pneumonia after AMI, so the potential benefits of IMT for these patients may have been neglected. We will focus on the improvement of inspiratory muscle strength after 30 days of training. In addition, we will record the clinical adverse events and the satisfaction of these patients and try to determine whether IMT has a potential benefit for decreasing incidence of pneumonia, MACE and length of stay (LOS), and also determine if IMT could benefit pulmonary function and quality of life.

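### Length of stay has no 30-day window and no rule for death, so an early in-hospital death would count as a short, favourable stay

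*Protocol article*

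**What the plan says.** The whole definition, under Length of Stay (LOS) in the protocol article, is: "Length of stay will be assessed by calculating the number of days the patient is in the hospital".

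The Discussion sets the direction of benefit. The investigators will "try to determine whether IMT has a potential benefit for decreasing incidence of pneumonia, MACE and length of stay (LOS"; a shorter stay is therefore the favourable result.

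The neighbouring clinical endpoints do have a time frame. Pneumonia is followed to day 30, and "MACE will be defined as all-cause death, recurrence of myocardial infarction, or stroke at 30 days post-randomization". Length of stay has none.

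Two other places bear on the point:

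- **Data Analysis** names no method for length of stay. The general rules apply: a t-test or analysis of variance if the data are normal, otherwise a Wilcoxon rank-sum test.
- **Assessment and Reporting of Adverse Events** records deaths both in hospital and afterwards, but restricts the end-of-study safety analysis to patients who contributed a day or more of safety data after discharge.

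**The concern.** A count of hospital days treats leaving alive and dying as the same event, since both stop the count. When fewer days are read as better, an early death is rewarded. Training starts 12 to 24 h after primary PCI, and the Discussion acknowledges that safety evidence soon after infarction is thin. An endpoint that improves when patients die early is therefore awkward here: if one arm had more early deaths, its length of stay would look better for that reason alone.

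The endpoint has some weight in the design. Sample Size Calculation arrives at 14 per group after attrition, 28 in all, and then goes to 60 so that the secondary endpoints can be studied better. The other 32 places rest on endpoints such as this one.

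**Working it through.** **The plan's own figure.** The article states no expected stay, spread, death rate or readmission rate, so there is no length-of-stay figure to reproduce. Its sample size concerns maximal inspiratory pressure (MIP) and does reproduce: 2 × (12/15)² × (1.960 + 0.842)² = 10.05, rounded up to 11 per group, and 11/0.8 = 13.75, rounded up to 14. It does not bear on length of stay.

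**Inputs for the illustration.**

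- 30 patients per arm (article, Randomization).
- Follow-up to day 30 (article, Study Design).
- Mean stay L: assumed 7 days, range 5 to 14.
- One in-hospital death on day 3: assumed. Randomisation is taken to fall on the day of admission.

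**Formulas.** Replacing one typical patient by one who dies in hospital on day 3:

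- plain length of stay: the arm mean falls by (L − 3)/30, an apparent improvement;
- days alive and out of hospital to day 30: the typical patient scores 30 − L and the patient who died scores 0, so the arm mean falls by (30 − L)/30, a worsening.

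For L = 7 these are (7 − 3)/30 = 0.13 day better and (30 − 7)/30 = 23/30 = 0.77 day worse.

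| Assumed mean stay L | Apparent improvement in length of stay, one death | Same, three deaths | Worsening in days alive and out of hospital, one death |
|---|---|---|---|
| 5 days | 2/30 = 0.07 | 0.20 | 25/30 = 0.83 |
| 7 days | 4/30 = 0.13 | 0.40 | 23/30 = 0.77 |
| 10 days | 7/30 = 0.23 | 0.70 | 20/30 = 0.67 |
| 14 days | 11/30 = 0.37 | 1.10 | 16/30 = 0.53 |

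**Scale.** With 30 per arm, two-sided 5% and 80% power, the detectable difference is SD × √(2/30) × 2.80. That is 1.45 days for an assumed SD of 2 and 3.62 days for an SD of 5. One death at L = 7 is thus 0.13/1.45 = 9% down to 0.13/3.62 = 4% of a detectable difference.

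**If the rank-sum test is used.** Stays are often skewed, so this is the likelier analysis. Suppose the patient who died has the shortest stay of all 60. That patient compares favourably with all 30 in the other arm; ranked worst, the same patient loses all 30 comparisons. The rank-sum (Mann–Whitney) statistic changes by 30. Its null standard deviation without ties is √(30 × 30 × 61/12) = √4575 = 67.6, so the scoring of one death moves the test by 30/67.6 = 0.44 standard deviations.

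**The case against.** The strongest reply has three parts.

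1. **Detail may sit elsewhere.** The article condenses a fuller protocol, and an analysis plan may exist. Rules for death and for the counting window are often placed there. This is fair: if those documents hold such a rule, the point is met. But the endpoint as published, combined with the stated direction of benefit, gives an early death a favourable value, and nothing shown changes that.
2. **Harm would be seen.** All-cause death is part of MACE, and the data safety committee reviews the in-hospital course. So early deaths would not go unnoticed. That does not alter the length-of-stay comparison, and the end-of-study safety analysis leaves out anyone who dies before discharge.
3. **The effect is small.** On the mean scale one death moves the result by a fraction of the detectable difference. This stands, and it limits the weight of the point.

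A reader might go further and infer that length of stay closes before IMT can act. The documents do not support this. The Discussion says "Previous studies have shown that IMT exceeding 2 weeks of therapy was effective for improving MIP (34", which concerns MIP and not hospital stay. It says a "shorter training time (< 10 days) still needs further investigation", which leaves the matter open. No expected stay is given. The home-based phase shows only that discharge is expected before day 30.

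A reader might also infer that readmissions are ignored. The text is silent, and its wording could include readmission days.

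**Conclusion.** The point holds as a small but real weakness in a secondary endpoint. As defined, length of stay has no window and gives an early in-hospital death one of the best values. Per day-3 death, with an assumed 7-day mean stay and 30 per arm, the arm mean improves by 0.13 day, where a death-aware measure would show 0.77 day worse. Across assumed stays of 5 to 14 days the figures are 0.07 to 0.37 day better and 0.83 to 0.53 day worse. All of these rest on assumed stays and an assumed death; the article supplies neither.

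It would be too strong to say that the endpoint cannot answer its question. The stated aim is exploratory, deaths are reported in MACE, and with few or no early deaths the distortion would be slight. The primary endpoint is unaffected.

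**What to change.** Choose one of these before any comparison by arm:

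- **Preferred:** compare the arms on days alive and out of hospital from randomisation to day 30. Days after death score 0 and readmission days are deducted. This settles window, death and readmission together.
- **Alternative:** keep length of stay, fix the rank-sum test for it, and rank in-hospital death as the worst outcome. This settles death only; the window and the counting of readmission days would still need a sentence.

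In either case report plain length of stay alongside.

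**Cost.** Deaths are already recorded and discharge dates are in the hospital record. The weekly calls and the day-30 visit exist, but the article does not say that they collect readmission dates, so those questions must be added for the preferred option. Days alive and out of hospital is less familiar, counts deaths that also appear in MACE, and can be moved noticeably by single deaths in 60 patients (0.77 day in an arm mean in the example). Plain length of stay shown next to it lets the reader see where a difference comes from.
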